## Abstract

**Background:**

Neonatal Acute Respiratory Distress Syndrome (NARDS) is a critical contributor to neonatal morbidity and mortality, with a global health burden that varies significantly by region. The Montreux definition provides a unified diagnostic framework; however, a significant clinical paradox exists. A prospective cohort in China reported a NARDS mortality rate of 12.6%, which is notably lower than the 17%–24% reported in a large-scale international prospective study. The underlying reasons for this discrepancy remain to be elucidated, whether due to differences in etiology, clinical practice, or patient demographics.

**Methods:**

The Shenzhen Neonatal ARDS Cohort Study (SZ-NARDS) is a prospective, multicenter observational cohort study spanning from 2025–2028, designed to address this knowledge gap. We will enroll more than 1,000 neonates who meet the Montreux criteria across nine tertiary neonatal intensive care units (NICUs) in Shenzhen, China. Longitudinal data collection includes granular clinical parameters, respiratory support metrics, and multi-modal biospecimens for deep phenotyping and multi-omics profiling. Survivors will undergo rigorous follow-up until 36 months' corrected age, with standardized neurodevelopmental, pulmonary, and growth assessments.

**Results:**

The primary objective of this study is to characterize the epidemiology of NARDS in this regional population and to test the following hypotheses: (1) The true incidence, etiology, and mortality rates of NARDS in Shenzhen will differ from existing international and Chinese cohorts, and these differences can be systematically explained by specific clinical and demographic factors. A multi-modal predictive model that integrates early clinical variables with multi-omics biomarkers has the potential to accurately identify neonates at high risk for severe NARDS [oxygenation index (OI) ≥ 16] and long-term adverse outcomes [Area Under the Receiver Operating Characteristic Curve (AUROC) > 0.85].

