**Conclusions:**

The SZ-NARDS cohort is uniquely positioned to resolve a major clinical contradiction in NARDS epidemiology. By integrating deep phenotyping with a longitudinal biobank and advanced machine learning algorithms, this initiative will generate a comprehensive dataset. This dataset will serve to refine existing prognostic models, identify regional disparities in disease biology, and inform the development of precision medicine interventions for this vulnerable population.

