The Montreux definition for NARDS, which was introduced in 2017, signified the initial phase of NARDS research, with a predominant focus on clinical and investigative purposes (6). Following the study protocol, the second phase of this project involves a prospective cohort study with two primary aims: first, to determine the prevalence of NARDS; and second, to characterize the epidemiology, clinical progression, treatment, and outcomes of neonates meeting the Montreux criteria. This methodological approach mirrors the processes followed after the establishment of the Berlin definition of ARDS for adults and the Pediatric Acute Lung Injury Consensus definitions for children (4, 13). However, it is noteworthy that no large-scale international NARDS registry has been established, with only two prospective cohort studies currently available. De Luca et al. (2022) (8) conducted the first international multicenter study, reporting a NARDS prevalence of 1.5% and a mortality rate of 17%–24%. They identified sepsis, aspiration syndromes, and pneumonia as the leading etiologies. Similarly, in 2023, Long Chen et al. (14) conducted a multicenter study in China, which reported a comparable prevalence (1.44%) but a strikingly lower mortality rate (12.6%), with pneumonia, asphyxia, and early-onset neonatal sepsis as the predominant causes. These findings underscore not only regional variations in NARDS prevalence, mortality, and etiological factors, but also reveal a critical clinical paradox: why does NARDS mortality in China appear significantly lower than the international average? Potential explanations for this discrepancy remain unexplored and may include: (1) differences in etiological distributions (e.g., a higher proportion of direct vs. indirect lung injury in Chinese cohorts); (2) variations in clinical management strategies (e.g., surfactant use, ventilation protocols); or (3) demographic factors (e.g., gestational age profiles, access to tertiary care). Resolving this contradiction is essential for refining our global understanding of NARDS pathophysiology and optimizing resource allocation. Nevertheless, a notable limitation in these studies was their emphasis on etiology and short-term outcomes, offering scant insight into the longer-term implications of the condition. To address these gaps, our study undertakes a 3-year, large-scale, multicenter cohort investigation. It will place particular emphasis on the long-term follow-up of patients at high risk of mortality and explicitly aim to dissect the drivers of the observed regional mortality disparity. This will offer a more comprehensive understanding of the natural history of NARDS, thereby expanding the current body of literature and providing mechanistic insights into how the Montreux definition applies across diverse healthcare settings.

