### Study design and setting

3.1

The SZ-NARDS registry is a prospective, multicenter, observational cohort study, scheduled to run from January 1, 2025, to December 31, 2028. This study will be conducted across nine tertiary-level NICUs in Shenzhen, China, selected for their infrastructure, expertise in neonatal critical care, and patient volume to represent a broad spectrum of care in the region. The study protocol is reported in accordance with the Strengthening the Reporting of Observational Studies in Epidemiology (STROBE) guidelines (30) (Supplementary Material 1). An overview of the study design is provided in Figure 1.

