### In-hospital outcomes

4.1

Primary in-hospital outcome: composite of mortality or requirement for ECMO within 28 days of NARDS diagnosis.Secondary in-hospital outcomes include: 28-day mortality; 28-day ventilator-free days; duration of invasive mechanical ventilation; incidence of BPD, severe pulmonary hemorrhage, and air leak syndromes; and incidence of significant non-pulmonary organ dysfunction, including hsPDA, NEC (stage ≥ II), and severe IVH (grade ≥ III).

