### Control of confounding and subgroup analyses

6.5

Multivariable models will adjust for key covariates (gestational age in completed weeks, birth weight z-score, sex, major comorbidities). We will perform stratified analyses by gestational age (<32 weeks, 32–36 weeks, ≥37 weeks) and present both adjusted and stratified effect estimates. To address prematurity as a potential source of confounding and misclassification (NRDS vs. NARDS), the central adjudication committee will review all ambiguous preterm cases, evaluating the timing of respiratory failure onset, radiographic features, surfactant exposure/response, and clinical course. For non-randomized treatment comparisons (e.g., ventilation strategies, surfactant use), we will use propensity score methods (matching, inverse probability weighting) and, when appropriate, instrumental variable approaches to reduce treatment selection bias. Sensitivity analyses will include restriction to term infants and to preterm strata to evaluate effect modification by prematurity.

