From a methodological standpoint, we have emphasized scientific rigor and reliability. The Montreux criteria specify exact radiographic, oxygenation, and timing requirements, which we enforce via training and central review to ensure consistent case ascertainment. Strict inclusion/exclusion criteria (e.g., excluding primary surfactant-deficiency RDS or transient tachypnea) maximize diagnostic specificity. Data are collected through a unified electronic system with built-in consistency checks, and periodic audits will monitor data quality. These measures minimize misclassification and bias. While treatment paradigms are not standardized, allowing for the capture of real-world practice variation for comparative effectiveness research, all procedures for diagnosis, data collection, and outcome assessment are rigorously harmonized across centers using detailed Standard Operating Procedures (SOPs). In summary, SZ-NARDS applies rigorous and harmonized procedures to ensure its findings are robust and reproducible.

SZ-NARDS will also supplement and extend previous findings. The international cohort by De Luca et al. reported a NARDS prevalence of 1.5% and survival rates of roughly 83% at 30 days (8). Our registry will test these figures in China: for example, early data from SZ-NARDS already suggest a somewhat higher incidence than the global average, possibly reflecting broader inclusion of perinatal cases. Similarly, Chinese prospective work found lower mortality (12.6%) (14) than the international study (17%–24%) (8), perhaps due to different case mix or care settings. By enrolling infants throughout Shenzhen, SZ-NARDS will help clarify the true NARDS mortality in China and explore reasons for any discrepancies. Compared with Chen et al.'s single-center retrospective, our prospective design will allow more accurate capture of risk factors (e.g., infection, birth complications) and outcomes. In addition, the Luo et al. study (*N* = 925, largely preterm) found that ARDS was mostly a late-preterm phenomenon and often managed with inhaled nitric oxide (41). SZ-NARDS will examine whether these patterns hold in a broader population including term infants.

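### The claim to explain mortality differences from published cohorts rests on analyses that all stay inside the Shenzhen cohort

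*Protocol article*

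**What the plan says.** The Results paragraph of the abstract places two hypotheses within the primary objective. The first is that Shenzhen rates "will differ from existing international and Chinese cohorts, and these differences can be systematically explained by specific clinical and demographic factors". The Introduction says the study will "explicitly aim to dissect the drivers of the observed regional mortality disparity" and lists three candidate explanations: etiological mix, clinical management and demographics. The abstract's conclusions call the cohort "uniquely positioned to resolve a major clinical contradiction in NARDS epidemiology".

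Other parts are more modest. Section 2.1 gives the primary objective as setting up a registry that describes epidemiology, phenotypes and outcomes. The Discussion speaks of looking into reasons for any discrepancies.

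On design, section 3.1 states: "This study will be conducted across nine tertiary-level NICUs in Shenzhen, China". All participants meet the Montreux criteria (section 3.6.1). On analysis, section 6.5 states: "Multivariable models will adjust for key covariates (gestational age in completed weeks, birth weight z-score, sex, major comorbidities".

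On outcomes, the primary in-hospital outcome is the "composite of mortality or requirement for ECMO within 28 days of NARDS diagnosis", and 28-day mortality without ECMO is secondary (section 4.1). The international study is said in the Introduction to have mortality of 17% to 24%, and in the Discussion to have "reported a NARDS prevalence of 1.5% and survival rates of roughly 83% at 30 days". The Chinese figure is 12.6%, with no time window given.

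**The concern.** Explaining a difference between two cohorts requires the case mix or care of both to be set against each other. The three explanations offered in the Introduction are all of this kind: each says that some factor is distributed differently, or acts differently, in China and elsewhere. A factor that strongly predicts death in Shenzhen explains none of the gap if it is equally common, with the same effect, in the comparator. No analysis named in section 6 brings in the comparator's distribution of anything.

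At stake is the study's headline reading. Adjusted odds ratios for death among Shenzhen infants could be presented as the drivers of the regional disparity. The published contradiction could then be taken as settled when the analysis had not addressed it.

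**Working it through.** **1. What each stated method can contrast.**

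| Section | Method | Contrast available |
|---|---|---|
| 6.1 | Group tests, logistic regression | Shenzhen infants with each other |
| 6.2–6.3 | Machine learning and its validation | Predicted risk among Shenzhen infants |
| 6.4 | Multi-omics classifiers | Shenzhen infants with each other |
| 6.5 | Covariate adjustment, gestational-age strata, propensity and instrumental-variable methods | Subgroups and treatments within Shenzhen |

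Cohort membership is constant in every row, so no row can apportion a difference between cohorts. Standardisation to published case mix, decomposition, and pooling with outside data are not named.

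**2. The plan's own sample size.** Section 3.6.2 takes 10 events for each of 10 predictors, so 100 deaths, at 12.6% mortality: 100 / 0.126 = 793.65, rounded up to 794. This reproduces the stated figure. It serves a prediction model for in-hospital mortality and does not bear on a between-cohort comparison.

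**3. Precision of the crude comparison.** Inputs: 1,000 Shenzhen infants (section 3.6.2); Shenzhen mortality of 12.6% (assumption, the plan's own planning rate); 239 infants in the international cohort (Discussion); international mortality of 17% and 24% (Introduction), with 20%, the approximate global figure in the Introduction, between them.

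SE = sqrt[0.126 × 0.874 / 1000 + p(1 − p) / 239]; 95% CI = (p − 0.126) ± 1.96 × SE.

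| International p | SE | Difference (points) | 95% CI |
|---|---|---|---|
| 17% | 0.0265 | 4.4 | −0.8 to 9.6 |
| 20% | 0.0279 | 7.4 | 1.9 to 12.9 |
| 24% | 0.0296 | 11.4 | 5.6 to 17.2 |

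Most of the uncertainty comes from the comparator. At 17% its own half-width is 1.96 × sqrt(0.17 × 0.83 / 239) = 4.8 points, so more Shenzhen infants would narrow the interval only slightly. If 17% were treated as an error-free benchmark, power would appear to be about 98%. With the comparator's error included it is about 44%. At 20% and 24% it is about 82% and 98.5%.

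**4. Illustration of case mix (all inputs assumed, none from the documents).** Let both cohorts have the same mortality within severity class: 5% mild, 12% moderate, 35% severe.

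- Mix 50/35/15: 0.50 × 5 + 0.35 × 12 + 0.15 × 35 = 11.95%.
- Mix 35/35/30: 0.35 × 5 + 0.35 × 12 + 0.30 × 35 = 16.45%.

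The crude rates differ by 4.5 points with identical outcomes at every severity. This shows only that a crude gap of this size can arise from mix alone. It says nothing about whether it does here.

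**5. Time window.** The international 17% corresponds to the 30-day survival of about 83%, while the Shenzhen outcome is at 28 days. If 1% to 5% of deaths fell on days 29 and 30 (assumption), 17% would become 16.8% to 16.2%. The effect is small.

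**The case against.** The strongest reply is that this is a condensed article, and section 6.6 says an analysis plan has been reviewed and approved. A standardised comparison could be in it. That has weight for any missing detail, but the point here concerns what is printed. The article names its methods down to particular imputation and multi-omics techniques, and those methods do not deliver the first hypothesis in its abstract.

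A second reply is that the formal objectives never promise an explanation: section 2.1 is descriptive, and the Discussion only proposes to look into reasons. This stands, and it shows that suitable wording is already in the document. It does not remove the stronger wording from the abstract and Introduction.

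Three stronger readings are tempting and are not supported.

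- A reader might infer that the design itself cannot address the question. The limit applies to the stated within-cohort models. Montreux severity (section 3.6.1), gestational age (Table 1) and direct or indirect cause (section 3.8.4) are collected, so standardisation to published case mix could address it in part.
- A reader might infer that mismatched mortality definitions invalidate the comparison. But 28-day mortality without ECMO is already an outcome, date of death is recorded in follow-up (Table 1), and nothing proposes using the ECMO composite across cohorts. A mismatch is shown for the international cohort only, since the window of the Chinese 12.6% is not given.
- A reader might infer from the 17% row that no difference could be shown. At 20% and 24% the interval excludes zero.

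**Conclusion.** The point holds in a limited form. The explanatory claims in the abstract and Introduction go beyond the analyses stated in section 6, all of which hold cohort membership constant. The registry and prediction aims are unaffected.

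That conclusion rests on the text alone and needs no numerical assumption. The precision figures assume Shenzhen mortality of 12.6% in 1,000 infants and a comparator of 239. They should be read over the whole range, from an interval that includes zero at 17% to one well clear of it at 24%. They concern whether a difference can be detected, which is a separate matter from whether it can be explained. Whether the comparators published usable case-mix distributions cannot be checked from this document.

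**What to change.** 1. Reword the first hypothesis in the abstract, the aim in the Introduction and the abstract's conclusion as a descriptive comparison with published cohorts, in line with section 2.1 and the softer wording in the Discussion.
2. Add to section 6 Shenzhen all-cause mortality, without ECMO, standardised to each comparator's published distribution of Montreux severity, gestational age and direct or indirect cause, where available. Give intervals that include the comparator's sampling error, and call the remainder unexplained.
3. State the expected precision over the full quoted range, 17% to 24%.
4. As a minor addition, report mortality on each comparator's own window beside the 28-day figure: 30 days for the international cohort, and for the Chinese cohort whatever window its 12.6% refers to, which should be stated.

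The cost is protocol wording and one extra table from data already being collected. The downsides are a more modest headline claim and standardisation limited to the factors that the comparators published.

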### Biomarker and predictive modeling outcomes

4.3

The primary outcomes related to the multi-omics biomarker analysis are:
The identification and validation of a proteomic and/or metabolomic signature, derived from baseline (within 24 h of diagnosis) plasma/serum samples, that demonstrates high accuracy [defined as an Area Under the Receiver Operating Characteristic Curve (AUROC) > 0.85] for predicting the development of severe NARDS (OI ≥ 16) within 72 h of diagnosisThe discovery of novel genetic variants *via* a Genome-Wide Association Study (GWAS) that are significantly associated with susceptibility to NARDS and/or in-hospital mortality.

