### Machine learning and predictive modeling

6.2

Beyond conventional regression, predictive modeling will employ a suite of algorithms, including penalized logistic regression (Elastic Net), decision trees, random forests, gradient boosting machines, support vector machines, and artificial neural networks. Two primary prediction tasks will be addressed: Early identification of neonates at risk of severe NARDS (OI > 16 within 72 h of diagnosis); Long-term prognosis (mortality, NDI, SRM, or growth restriction at the 24- and 36-month corrected age). Candidate predictors will be selected based on clinical relevance and temporal availability (within 24 h for early warning models; within 7 days for prognostic models). Feature selection and regularization will primarily use Elastic Net. To identify novel NARDS endotypes, Integrative Multi-Omics Factor Analysis (MOFA) or similar unsupervised data integration approaches [e.g., sparse Partial Least Squares Discriminant Analysis (sPLS-DA)] will be employed to identify latent factors and co-varying molecular pathways across omics layers. These integrated molecular signatures will subsequently serve as input features for downstream machine learning models (e.g., Random Forest) to construct highly discriminative and biologically informed predictive classifiers.

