### Model evaluation and validation

6.3

Model performance will be evaluated using the area under the receiver operating characteristic curve (AUROC), sensitivity, specificity, calibration plots, Brier score, and, where applicable, precision–recall curves for imbalanced outcomes. Internal validation will be performed using a robust strategy: randomly partitioning the cohort into a 70% Discovery Set and a 30% Internal Validation Set at baseline. The validation set will serve as an independent internal check for model generalizability. We will also perform internal validation using cross-validation and bootstrap resampling, strictly adhering to the TRIPOD reporting guidelines for predictive models (38). Where feasible, temporal or center-level external validation (or internal holdout by center) will be undertaken to assess generalizability.

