### Multi-omics integration and validation

6.4

Biomarker discovery will follow a split-sample design, with the cohort randomly divided into a training set (70%) and an independent validation set (30%). Within each omics layer, initial feature selection will be conducted using multivariate analytical techniques such as PLS-DA. Subsequently, integrative multi-omics analyses will be performed using the DIABLO framework (Data Integration Analysis for Biomarker Discovery using a Longitudinal Approach) to construct predictive models that integrate molecular and clinical data. Model performance will be evaluated in the validation set using AUROC, sensitivity, specificity, and calibration metrics, ensuring rigorous validation of biomarker-based classifiers.

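### The AUROC > 0.85 criterion for the integrated clinical-plus-omics model has no clinical-only reference, so it can be met when the omics add nothing

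*Protocol article*

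**What the plan says.** The Abstract (Results) sets out a hypothesis that "A multi-modal predictive model that integrates early clinical variables with multi-omics biomarkers has the potential to accurately identify neonates at high risk". The targets are severe NARDS, defined as OI of at least 16, and "long-term adverse outcomes [Area Under the Receiver Operating Characteristic Curve (AUROC) > 0.85". That threshold is the only numerical standard attached to the hypothesis.

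Section 4.3 uses the same threshold for a different object. This is a proteomic and/or metabolomic signature from baseline plasma or serum "that demonstrates high accuracy [defined as an Area Under the Receiver Operating Characteristic Curve (AUROC) > 0.85" for severe NARDS within 72 h of diagnosis.

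Section 6.2 allows predictors by time of availability: "within 24 h for early warning models; within 7 days for prognostic models". Section 6.4 then uses an integration framework "to construct predictive models that integrate molecular and clinical data", "with the cohort randomly divided into a training set (70%) and an independent validation set (30" per cent).

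On evaluation, Section 6.3 says "Model performance will be evaluated using the area under the receiver operating characteristic curve (AUROC), sensitivity, specificity, calibration plots, Brier score" and adds precision-recall curves. Section 6.4 says "Model performance will be evaluated in the validation set using AUROC, sensitivity, specificity, and calibration metrics". Only AUROC carries a threshold. The article names no clinical-only reference model, no difference between models and no other measure of incremental value.

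**The concern.** The criterion takes the total discrimination of the combined model as its input. It does not isolate what the molecular data contribute.

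For the early outcome this matters in practice. Section 3.6.1 makes OI of at least 4 an entry criterion, so every infant's OI is known at diagnosis. Table 1 lists respiratory support parameters and blood gas analysis among the day 1 data. The outcome is a later value of the same index crossing 16. A strong predictor may therefore be on the chart before any assay is run.

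The Introduction justifies biomarkers by the improvement they might bring to prediction, and Section 6.2 expects classifiers informed by biology. Under the stated criterion the study could report such a classifier as confirmed when all of its discrimination comes from bedside values.

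**Working it through.** **The article's own figure.** Section 3.6.2 asks for 10 events for each of 10 predictors, so 100 deaths. At 12.6% mortality, 100 / 0.126 = 793.65, rounded up to 794. It reproduces, but it concerns the mortality model and does not bear on the AUROC criterion.

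**Inputs from the article.** Target 1,000 infants; 30% validation set, 0.30 × 1,000 = 300; entry at OI ≥ 4; event at OI ≥ 16; criterion AUROC > 0.85.

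**Inputs assumed, because the article does not give them.** The OI distribution at diagnosis, the correlation of baseline with later OI, the severe-NARDS rate and the clinical-only AUROC.

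**Check 1: baseline OI as the only informative predictor.** Log OI at diagnosis is normal (median 8 to 10, SD 0.55 to 0.60), truncated at OI ≥ 4. Later log OI = baseline log OI + N(0, s), with s between 0.2 and 0.8. The event is later OI ≥ 16. The omics effect is zero, so baseline OI alone stands in for the integrated model. Only infants with OI < 16 at diagnosis are kept, about 230 to 265 of the 300.

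| Correlation, baseline with later log OI | AUROC of baseline OI | Share of validation sets with AUROC > 0.85 |
|---|---|---|
| about 0.77 | 0.88-0.90 | about 80-95% |
| about 0.67 | 0.83-0.85 | about 25-55% |
| about 0.58 | 0.78-0.81 | about 3-12% |
| 0.40-0.52 | 0.69-0.77 | almost never |

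**Check 2: an integrated model that contains noise features.** N = 1,000, split 70/30. A logistic model is fitted to one clinical score plus five pure-noise omics features, with 1,000 runs per setting and severe-NARDS rates of 20%, 30% and 40%.

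| True clinical-only AUROC | Integrated model exceeds 0.85 |
|---|---|
| 0.80 | 1-3% |
| 0.83 | 18-21% |
| 0.85 | 44-47% |
| 0.87 | 76-80% |
| 0.90 | 97-99.5% |

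The mean AUROC difference, integrated minus clinical-only, lay between -0.004 and -0.002 in every setting. A paired comparison would on average show no gain in the settings where the absolute criterion is usually met.

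**Analytic cross-check (Hanley-McNeil).** SE² = [A(1−A) + (n1−1)(Q1−A²) + (n0−1)(Q2−A²)] / (n1·n0), with Q1 = A/(2−A) and Q2 = 2A²/(1+A). Take A = 0.87, n1 = 60, n0 = 240:
- Q1 = 0.7699, Q2 = 0.8095, A² = 0.7569.
- The numerator is 0.1131 + 59 × 0.0130 + 239 × 0.0526 ≈ 13.46.
- SE = √(13.46 / 14,400) = 0.0306.
- P(AUROC > 0.85) = Φ(0.02 / 0.0306) = 0.74, close to the 76% simulated at a 20% event rate.

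**The case against.** **The hypothesis claims accuracy, not improvement.** The Abstract says the model may identify high-risk infants accurately, and an absolute AUROC does measure that. Objectives 2.2.2 and 2.2.3 speak of developing, discovering and validating. This is fair: the criterion is valid for the combined model's accuracy. It does not support a statement that the omics contribute.

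**Section 4.3.** A reader might infer that its signature could also pass on noise. It could not. As written it is built from proteins and metabolites only, so uninformative omics would give an AUROC near 0.5 and fail. The narrower point is that passing would show the signature predicts, not that it adds to OI or gestational age.

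**The whole cohort.** A reader might infer that the criterion would nearly always be met in the cohort as enrolled, even when baseline and later OI are only moderately correlated. That requires counting infants already severe at diagnosis as events. Without that, the criterion is met in about 0% of sets at correlations of 0.50-0.55. How such infants are handled is a separate question, and no whole-cohort percentage is relied on here.

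**The size rests on assumptions.** This stands. The results run from almost never to about 95%, and they show a possibility, not a likelihood. Section 6.2 does not name OI as a predictor; its use is inferred from Section 3.6.1 and Table 1. The simulations concern severe NARDS only; the baseline-OI mechanism does not operate for the long-term outcomes.

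**Fewer than 300 infants may have omics.** Biospecimens are a voluntary sub-study (Section 3.8.2). This does not help the criterion. By the Hanley-McNeil formula, at a true AUROC of 0.80 and 30% events, the chance of exceeding 0.85 rises from 5.0% with 300 infants to 12.2% with 150.

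**The comparator may be in the analysis plan.** Section 6.6 refers to an approved plan that is not shown, and it may contain one. The point here is the success criterion that the article itself fixes.

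**Conclusion.** The point holds in a limited form. The integrated-model hypothesis is tied to an absolute AUROC above 0.85 for a model that already includes clinical variables, and the article specifies no clinical-only reference. Meeting the criterion therefore does not show that the omics contribute.

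The practical weight depends on an unknown. If early clinical data alone reach an AUROC near 0.88-0.90 among infants not yet severe, the criterion would be met about 80-95% of the time with worthless omics. If they reach only about 0.80, that would be uncommon, and below that almost unknown. These figures assume a log-normal OI, zero omics effect and up to 300 validation infants.

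The documents do not support a claim that false confirmation is likely, or that the Section 4.3 signature has the same fault. The correction is inexpensive and worth making before the models are fitted.

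**What to change.** In Sections 6.3 and 6.4:
- Prespecify a clinical-only benchmark model that includes OI at diagnosis, fitted in the same infants, with the same 70/30 split and resampling as the integrated model.
- Report the paired difference in validation AUROC with a 95% confidence interval, and the change in Brier score.
- Rest any statement that omics improve prediction on that difference and its interval.
- Keep AUROC above 0.85 as a description of the combined model's accuracy.
- In Section 4.3, say that meeting the threshold shows prediction by the signature, not added value over OI or gestational age.

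An interval that includes zero should be read as inconclusive. Under assumed binormal scores, 15-30% events and 230 to 265 infants, a true gain from 0.85 to 0.88 would be detected only about 39-61% of the time, so the interval should not serve as proof that omics have no value.

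The cost is one extra model fit on data already collected, plus wording. The downside is that a claim of added omics value becomes harder to reach.
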